**Table 2: Configuration of the intervention to provide Youth-Friendly Services**

|                    |                                                                                                                                                                                                                                                                                                                                                                                                                                                                         |
|--------------------|-------------------------------------------------------------------------------------------------------------------------------------------------------------------------------------------------------------------------------------------------------------------------------------------------------------------------------------------------------------------------------------------------------------------------------------------------------------------------|
| Environment | 
 
• Convenient location
 
• Adequate and attractive space where youth can socialise
 
• Comfortable surroundings
 
• Configured to attract male youth and female (e.g. male and female service providers)
 
• Providers known by first names
 
• Encouragement of youth-focused “non-health” activities e.g. music, dancing, sport, games, talks
 
• Outreach - sensitisation
 
 |
|--------------------|-------------------------------------------------------------------------------------------------------------------------------------------------------------------------------------------------------------------------------------------------------------------------------------------------------------------------------------------------------------------------------------------------------------------------------------------------------------------------|

**Table 2 (continued): Configuration of the intervention to provide Youth-Friendly Services**

|                                            |                                                                                                                                                                                                                                                |
|--------------------------------------------|------------------------------------------------------------------------------------------------------------------------------------------------------------------------------------------------------------------------------------------------|
| Confidentiality and privacy         | 
 
• Visual and auditory privacy
 
• Names not mentioned/ recorded*
 
• Anonymity of service accessed*
 
                                                                            |
| Information                         | 
 
• Paper and electronic IEC materials (leaflets, posters, videos) appropriate for various age and literacy levels
 
                                                                             |
| Flexibility                         | 
 
• Services will be provided from 11am to 7pm and at weekends (e.g. CAPS groups)
 
• Drop-in service delivery (no appointments)
 
                                                        |
| Youth as equal partners             | 
 
• Youth involved in design of space and intervention content and delivery
 
• Youth Advisory Board for feedback
 
                                                                       |
| Appropriate and affordable services | 
 
• Wide range of services available (see above)
 
• Services free of charge
 
• System to “red-flag” youth with concerns
 
• Well-established linkages to other services
 
 |

*\*except where required for clinical care e.g. registration with national HIV care programme*

The intervention team will consist of a nurse, CHW and youth workers. The team will consist of a mix of male and female providers. There will be one intervention team per province, each responsible for delivering the intervention to 4 clusters. Each intervention team will rotate around its allocated clusters on a weekly basis (one day a week per cluster). Although the intervention teams are affiliated with this research project (and this will be made clear to all those who interact with them), their role will be to primarily to deliver what is recognized by the WHO as a ‘best practice’ public health intervention. Hence for this project we regard the intervention teams as separate from the ‘research teams’ and believe that the norms and standards governing their activities should largely be those accepted

for the implementation of public health interventions rather than those applied to conventional clinical research projects.

The intervention team will be selected on the basis of prior experience of working in communities and with youth. In addition, the intervention team will undergo a training programme on provision of youth friendly services as well as on each of the intervention components. Training will particularly focus on the following aspects:

1. Adolescent physiology and development
2. Knowledge and skill on delivery of each intervention component according to age and maturity of client
3. Referral pathways
4. Skills on counselling and communication with youth
5. Skills to bring myths to surface, to discuss and dispel them
6. Interpersonal skills
7. Attitudinal training (respect, confidentiality, non-judgement, relatability)

#### **ii. 3.3.2 Collaborations and partnerships**

The study team will collaborate with partners to facilitate an adequate supply of condoms, STI treatment, contraception, MHM products, clinical supplies including blood tests and drugs for individuals with HIV; and approval of use of health centre data.

### **• 4. Study Population**

#### ***h. 4.1 Selection of Study Clusters***

The study will be conducted in 3 provinces: Harare, Bulawayo and Mashonaland East. Harare is the capital and largest city and the population is predominantly of Shona ethnicity; Bulawayo, the second largest city in the country is situated about 450km west of Harare and is predominantly Ndebele. Mashonaland East borders Harare and peri-urban settings in this province were selected.

The first stage of the cluster selection was to define the criteria / requirements for each cluster. These were defined by the Trial Management Team as:

- An estimated cluster size of between 2000 – 4000 youth (to get a *minimum of 1500* young people). This population size would allow for overestimates from census data, migration and so on.
- A cluster to be served by a defined clinic, and the clinic not serving another cluster.  
The clinic would ideally be sited within the cluster, but not necessarily so.
- Geographical separation between clusters to minimise contamination.
- Each cluster in an urban or peri-urban setting (as population densities in rural areas are very low)

Geographical Information (GIS) data which included spatial and attribute datasets (tabular data) were provided for the study area by the Zimbabwe

Electoral Commission. These included: electoral wards (with the population), health centres (with names and type), and schools (with name and type). The population for the study area was based on the Zimbabwe 2012 Census. The population within the study age group was assumed to be 20% of the total population based on the 2012 Census percent composition of the population (15-19yrs: 10.8% and 20-24yrs: 9.2%).

These data and local field knowledge were used to define a list of possible locations for clusters. The rough locations were examined in more detail, overlaying ward populations, clinic and school locations on top of Openstreetmap data which shows the roads, rivers, and, for some locations, all buildings. The actual cluster was defined by taking the electoral ward boundaries as starting points, to identify areas within the required population range required. These areas were then modified to take into account natural breaks for e.g. a river or a major road to provide sensible cluster boundaries. Where possible, natural boundaries such as a green space or industrial areas, were used to form the edge of the cluster to minimise contamination. In some areas, where wards contained far large populations than 4000 young people and where all buildings were mapped, simple population estimation was carried out. This took the total number of buildings and multiplied it by 5.6 (a standard number used across Sub-Saharan Africa). This method of estimation was used to define an area that would contain between 2000-4000 young people. Once all the clusters were defined the boundaries and their clinics were exported to Google Earth (.kml format), to enable field teams to check the clinic locations and for key POIs to be mapped.

For mapping key POIs, the field team will walk around the entire cluster, marking any point of interest onto a print out of the openstreetmap data while at the same time storing the location and details as a bookmark in MAPSME. The electronic locations will be validated against the paper version locations.

#### ***i. 4.2 Randomisation***

The first step in randomisation will be to obtain agreement from communities to take part in the study. Twenty-four clusters will be randomly allocated 1:1 to the intervention and standard of care arms. All clusters will be of approximately equal population size as a result of the mapping process used to define them. We will randomise clusters within each of three strata, defined by i) whether they receive healthcare from Harare municipal services (Harare City Health), Bulawayo municipal services (Bulawayo) or non-municipal (MoHCC) services (Mashonaland East), ii) HIV prevalence and iii) viral suppression.. We will aim for equal numbers of clusters per stratum although this will depend on availability of suitable clusters/stratum. Within each of the 3 strata, we will randomise 1:1 to the control or intervention arm

**Figure 3: HIV prevalence among 15-64 year olds by province (ZIMPHIA estimates)**

[figure not shown]

**Figure 4: VL suppression (VLS) among 15-64 PHIV year olds by province (ZIMPHIA estimates)**

[figure not shown]

To maximise transparency and buy-in from stakeholders, a semi-public randomisation procedure will be carried out with representatives of the community, MoHCC and respective City Health or town council health departments.. After initiation of the intervention, if any community needs to be removed from the study (e.g. if a community should cease to agree to participate in the study) then the study leadership will decide upon the most appropriate course of action, which would likely include replacement of the community.

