### ***d. 2.3 Study design***

A cluster randomised trial design will be used to address the objectives of the study. The study will be conducted in three provinces of Zimbabwe (Harare, Bulawayo and Mashonaland East). A total of 24 study clusters, stratified by province, will be randomised in a 1:1 allocation ratio to one of the following two arms:

- i. Control Arm - Existing HIV and SRH services
- ii. Intervention Arm - Community-based intervention

The target population for the intervention will be individuals aged 16-24 years. In Zimbabwe, individuals aged 16 years and older are able to access SRH and HIV services without guardian consent.

The definition of a cluster, cluster selection and the randomisation method are described in Section 4.2. A pilot will be conducted to test the relevance, acceptability and feasibility of the intervention components, and to optimise trial procedures. The pilot will be delivered over a three-month period in one of the trial clusters in Harare. Iterative loops of evaluation will be used to refine the intervention procedures during the pilot phase.

The intervention will be implemented over a 30 month period in each cluster. This is an extension of six months beyond the originally planned 24 months to mitigate against the effects of the COVID19-related lockdowns during which service provision was not feasible. At the end of this period, a population cross-sectional survey will be conducted to ascertain outcomes. The deployment of the intervention will occur in phases with 4 clusters implementing the intervention first, followed by the next 4 clusters 3 months later and the final 4 clusters starting a further 3 months later. The intervention will be implemented in phases to ensure that the final survey is completed within three months of the end of the intervention.

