The local health services (e.g. the primary health care clinics) are the custodian of health of the community and collaboration with them is essential for ensuring both care of CHIEDZA clients beyond the intervention and to facilitate scalability. The intervention team will work with the nurses at the clinics to ensure that HIV and other services provided by CHIEDZA are integrated with routine services e.g. ensuring that all youth diagnosed with HIV through CHIEDZA are registered into the National ART programme. Regular meetings will be held between the intervention team and health facility staff to ensure that strong relations are maintained.

In addition, a key aspect of building confidence within communities is the knowledge that the study is being conducted in partnership and with the support of the government. Partnership with the MoHCC was sought at the inception of the study and input on the proposal was given by the MoHCC before the grant was submitted; the Deputy Director of the AIDS and TB Unit at MoHCC is a project co-investigator. Support and permission to conduct the study will be sought from

the Provincial Medical Directorate, District Medical Officers, Local Authorities, Health Services Directors and Town Secretaries for the smaller towns which do not have directors of Health Services. At community level, permission will be sought from the Provincial and District Administrators for use of community centres.

- **5. Research Procedures and Activities**

- k. 5.1 Prevalence survey**

A community cross-sectional survey will be conducted among 18-24 year olds after 30 months of implementation of the intervention (700 randomly selected youth per cluster). The age group has been selected to ensure maximum exposure to the intervention, and to include only those able to give independent consent. A pre-intervention survey with HIV testing will not be conducted as this would itself constitute a mass testing programme and may compromise the anticipated intervention effect. The prevalence survey team will be separate from the intervention team, and will be blinded to whether the cluster is an intervention versus control cluster. However, the possibility of the survey team identifying the trial arm allocation for a particular cluster from other sources cannot be excluded.

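### Section 4.2 makes replacement the likely response when a community leaves after the intervention starts, with no rule for selecting, allocating or analysing the clusters involved

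*Combined protocol and SAP*

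**What the plan says.** Section 4.2 (Randomisation) sets the design: "Twenty-four clusters will be randomly allocated 1:1 to the intervention and standard of care arms", and "Within each of the 3 strata, we will randomise 1:1 to the control or intervention arm". Allocation is not concealed afterwards, since "a semi-public randomisation procedure will be carried out with representatives of the community" together with health authorities; section 8.5.2 describes the same event as a ceremony.

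The contingency closes section 4.2, after Figure 4. It begins "After initiation of the intervention, if any community needs to be removed from the study", gives withdrawal of a community's agreement as an example, and ends "the study leadership will decide upon the most appropriate course of action, which would likely include replacement of the community".

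Three other statements bear on it:

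- Section 2.3: "The intervention will be implemented over a 30 month period in each cluster", with the survey completed within three months of the end of the intervention.
- Section 5.1: "A pre-intervention survey with HIV testing will not be conducted". Outcomes come only from the endline survey of "700 randomly selected youth per cluster".
- Section 7.3: the primary analysis regresses cluster log risk on stratum and arm, and a CONSORT flowchart shows the clusters allocated. It has no rule for removed or added clusters and no explicit intention-to-treat statement; analysis by allocated arm is only implied.

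**The concern.** A cluster trial with 12 clusters per arm draws its protection against confounding from the random allocation of those 24 clusters. The clause lets their composition change after allocation is known, by a decision of people who know the arms, and no selection rule limits that decision.

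Removal could also depend on arm. Only intervention communities host the service. Control communities keep existing services and meet the study mainly through the survey and routine data collection. The reasons for leaving therefore need not be the same in the two arms.

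Without a baseline HIV survey, nobody could check whether a replacement resembled the cluster it replaced on the outcome. A replacement in the intervention arm would also start late. At stake is whether the primary risk ratio compares the randomised clusters or a set partly assembled afterwards.

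**Working it through.** **1. Reproduce the plan's power.** Inputs from section 7.2: 12 clusters per arm, m = 700 × 3% = 21 HIV-positive participants per cluster, p0 = 43%, p1 = 73%, coefficient of variation k = 0.25 to 0.30. Alpha is not stated; two-sided 0.05 is assumed, in line with the planned 95% CI.

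SE² = [p0(1−p0)/m + k²p0²]/c0 + [p1(1−p1)/m + k²p1²]/c1, with power from a non-central t on c0 + c1 − 2 degrees of freedom.

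At k = 0.30:

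- Control term: (0.2451/21 + 0.09 × 0.1849)/12 = 0.00236.
- Intervention term: (0.1971/21 + 0.09 × 0.5329)/12 = 0.00478.
- SE = √0.00714 = 0.0845, so 0.30/0.0845 = 3.55 on 22 df, which gives power 92.4%.

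At k = 0.25, SE = 0.0741, the ratio is 4.05 and power is 97.2%. Both agree with the stated figure of over 90%. The same formula reproduces Tables 6, 7 and 8 to rounding; for example, Table 7 comes out as 91.5, 81.5, 64.0 and 51.8% against the stated 92, 82, 64 and 52%.

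**2. Cost of not replacing** (43% versus 73%).

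| Situation | k = 0.25 | k = 0.30 |
|---|---|---|
| 12 v 12 clusters | 97.2% | 92.4% |
| One intervention cluster lost | 96.3% | 90.8% |
| One control cluster lost | 96.7% | 91.5% |
| One lost in each arm | 95.8% | 89.8% |
| Two intervention clusters lost | 95.2% | 88.7% |
| Withdrawn cluster kept in its arm at 43% | 94.9% | 88.5% |

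The last row assumes that the withdrawn cluster ends at the control level. The arm mean is then (11 × 73 + 43)/12 = 70.5%. That mean is put into the formula with the same k, so the row is approximate.

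**3. Effect of one swap.** The planned analysis works with geometric means, so exchanging one cluster of 12 multiplies the arm mean by (new risk/old risk)^(1/12). As an extreme illustration, take a removed cluster at the control level of 43% and a replacement at 70%:

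- (0.70/0.43)^(1/12) = 1.628^(1/12) = 1.04.
- On the arithmetic scale: (70 − 43)/12 = 2.25 points. Table 6's detectable differences at 700 per cluster and k = 0.25 are 21 points at 80% power (64 − 43) and 24 points at 90% power (67 − 43), so the shift is about a tenth of either.
- A replacement one or two between-cluster SDs above the cluster it replaces, (1 + k)^(1/12) or (1 + 2k)^(1/12): about 1.02 to 1.04.

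The STI comparison uses 16 clusters, 8 per arm, so one cluster carries one-eighth of an arm. The same 1.628 ratio would then give 1.628^(1/8) = 1.06.

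**4. Exposure.** An intervention-arm cluster that enters j months after its stratum began has 30 − j months when the intervention is due to end. The three-month survey round could absorb at most three months of that shortfall. Beyond this, either the planned exposure or the survey schedule has to give way.

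**The case against.** The strongest defence is that this is a conditional clause for an event that may never happen. The documents report no removal and no replacement. It would be tempting to conclude that the randomisation is broken; the text supports only that it would be compromised if the clause were used.

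A reader might also infer that the replacement would be hand-picked and known to be willing. The protocol says that the leadership chooses the course of action and is silent on how a replacement is selected. Willingness does not distinguish it either, because section 4.2 requires community agreement before randomisation. Withdrawal of agreement is an example, not the only trigger, and the clause covers either arm.

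A further tempting inference is that bias would run upward. Exchanging a reluctant intervention community for a receptive one could inflate the effect, but a late start would dilute it, and removals in the control arm could act either way. The net sign is unknown.

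Oversight exists: a steering committee with an independent chair advises on conduct (sections 8.7 and 10.4), and the flowchart would show allocations. Finally, a community that leaves the study, and does not merely stop hosting the service, may refuse the survey as well.

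These points limit the size and certainty of the harm. They do not supply the missing rule, and the text still names replacement as the likely course.

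**Conclusion.** The point stands as a weakness in a contingency that should be corrected before it is needed. It goes beyond missing detail, because the protocol points towards a course that is worse than an inexpensive alternative. If followed, it would put a cluster that was never randomised into the primary regression, with no rule on selection, arm, stratum, exposure or analysis.

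The numerical effect of one swap is probably modest: a factor of about 1.04 in the extreme illustration, somewhat more in the STI comparison, with direction unknown. Those figures rest on assumed cluster risks that the documents do not give.

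Replacement is not needed to hold the stated power if one cluster is lost; that power stays above 90% at both values of k. It does fall slightly below 90% at k = 0.30 if a withdrawn cluster is kept at control level, if one cluster is lost from each arm, or if two intervention clusters are lost.

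**What to change.** Replace the sentence in section 4.2, and repeat the rule in section 7.3, with wording such as:

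> After randomisation no cluster will be replaced in the primary analysis. A cluster that stops the intervention stays in its allocated arm, is surveyed at endline where the community and individuals permit, and is analysed as randomised. If the survey is not permitted, the analysis uses the remaining clusters, and the loss and its reason are reported by arm in the flowchart. Any added cluster is used only in a labelled sensitivity analysis.

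Surveying a cluster that no longer hosts the service is workable in principle: the survey team is separate from the intervention team, consent is individual, and control clusters are surveyed without hosting anything. The permission condition respects a community that withdraws altogether.

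The change itself is a few sentences. Its price is the power loss tabulated above: at most 1.6 points if one cluster cannot be surveyed, or 2.3 (k = 0.25) to 3.9 points (k = 0.30) if a withdrawn intervention cluster is retained at the assumed control-level outcome.

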#### ***j.* 4.3 Community Engagement**

This study will build on the community engagement established during the formative work for the CHIEDZA trial conducted between 2017-2018. Briefly, this comprised a detailed stakeholder analysis (meetings and discussions with stakeholders including health services, CBOs, NGOs), and interviews and discussions with youth, family members and other community gatekeepers.

These informed the choice of implementing partners for the intervention (e.g. partners to whom CHIEDZA clients will be referred to for specific services).

Workshops were held with youth selected from study communities to inform the design, content and delivery of the intervention and to ensure they are equitable partners in the research process. Workshop participants were identified through relevant CBOs, health facilities and through existing networks. Each stratum will be served by a YAG, selected from those who attend the workshops. The YAGs will provide guidance on the implementation of the intervention and on study procedures, and represent the views of youth- the beneficiaries of this research. Strong community engagement will allow the establishment of a partnership between communities, participants and researchers to ensure the latter discharge their responsibilities ethically in the study communities. Community engagement will be an ongoing process through regular contacts with stakeholders and the YAGs. A dedicated CHIEDZA community engagement team will work with various community groups and stakeholders such as churches, schools, law enforcement, government structures at community level, health-related committees, and development-related committees. The main role of the community engagement team is to maintain an ongoing dialogue between researchers and community groups. Engagement will be in the form of community meetings, workshops, participation in stakeholder meetings and relevant forums and importantly maintaining a regular presence in the intervention communities. This will enable the study management team to ensure that information about the study is disseminated widely in the communities involved and to keep the community stakeholders updated regarding progress of the study, events that may arise in conduct of the research, and new developments in HIV prevention and treatment. Community engagement will allow researchers to get feedback from the community on social harms, individual and community level risks, perceptions about the study and implementation challenges. The YAGs and the community engagement team will remain involved throughout the study. The YAG members and the community engagement team will be trained on GCP and research ethics.

The local health services (e.g. the primary health care clinics) are the custodian of health of the community and collaboration with them is essential for ensuring both care of CHIEDZA clients beyond the intervention and to facilitate scalability. The intervention team will work with the nurses at the clinics to ensure that HIV and other services provided by CHIEDZA are integrated with routine services e.g. ensuring that all youth diagnosed with HIV through CHIEDZA are registered into the National ART programme. Regular meetings will be held between the intervention team and health facility staff to ensure that strong relations are maintained.

In addition, a key aspect of building confidence within communities is the knowledge that the study is being conducted in partnership and with the support of the government. Partnership with the MoHCC was sought at the inception of the study and input on the proposal was given by the MoHCC before the grant was submitted; the Deputy Director of the AIDS and TB Unit at MoHCC is a project co-investigator. Support and permission to conduct the study will be sought from

the Provincial Medical Directorate, District Medical Officers, Local Authorities, Health Services Directors and Town Secretaries for the smaller towns which do not have directors of Health Services. At community level, permission will be sought from the Provincial and District Administrators for use of community centres.

- **5. Research Procedures and Activities**

- k. 5.1 Prevalence survey**

A community cross-sectional survey will be conducted among 18-24 year olds after 30 months of implementation of the intervention (700 randomly selected youth per cluster). The age group has been selected to ensure maximum exposure to the intervention, and to include only those able to give independent consent. A pre-intervention survey with HIV testing will not be conducted as this would itself constitute a mass testing programme and may compromise the anticipated intervention effect. The prevalence survey team will be separate from the intervention team, and will be blinded to whether the cluster is an intervention versus control cluster. However, the possibility of the survey team identifying the trial arm allocation for a particular cluster from other sources cannot be excluded.

The cross-sectional survey will be conducted in phases following the phased implementation of the intervention (Figure 3). Therefore, the first stratum of four clusters to implement the intervention and four control clusters will be surveyed over a three-month period. This will be followed by a survey of the intervention and control clusters in the second stratum over a period of three months. The clusters in the third stratum will then be surveyed. This will ensure that all intervention clusters are surveyed within a three-month period after the end of the intervention.

The sampling methodology will combine remote selection methodologies that use geographical information systems and satellite photographs and traditional random house selection. Very high-resolution satellite images are frequently updated in Zimbabwe, and will be used to map every building in the clusters into Openstreetmap. This will be done remotely during the early stages of the project. The resulting Openstreetmap data will be checked by the field teams during the POI mapping process.

ARCGIS will be used to select random geopoints (defined as a short stretch of a street: about 100-200m) within each cluster. More random geopoints than required will be selected to ensure that enough are available during the survey. All eligible individuals whose household is on either side of the street will be approached for participation in the study. Selecting every eligible household member gives a self-weighting sample as every individual has the same probability of selection. Selecting households with equal probability as described above and then selecting ALL youth in the selected households is the simplest form of self-weighting design. In the event that there are no eligible individuals in the household the team will move on to the street. Every household in the stretch of street will be visited until 700 participants are enrolled.

Using the list of roads in the cluster, the survey team will go street by street and visit every household on both sides of the street. All households in the designated stretch of the street will be visited to confirm that there is an eligible individual residing at the dwelling and if present to invite them to participate in the survey.

If the eligible individual is not present the field team will pre-book study interview time. The survey team will visit the household for the actual interview at the pre-booked time. If the eligible individual is not available on the booked appointment time and date, another appointment will be made for a second visit. If the individual is not available after three visits, no further attempts will be made for that individual. If the household is empty, then neighbours will be asked to provide information on the composition of the household. If it is clear that there are no eligible individuals living in the household, then the household will not be revisited. If there are or may be eligible individuals living in the household, then the household will be visited a further two times. If there is more than one eligible individual in the household, then all eligible individuals in that household will be enrolled.

Eligibility criteria will be:

- Age  $\geq$  18 years (day of their 18th birthday or older) to 24 years (one day before their 25th birthday)
- Written informed consent to complete the questionnaire and provide a blood sample

A study number will be allocated to each participant and a fingerprint will be collected. The fingerprints will be compared with the fingerprints of CHIEDZA service attendees to explore 1) the proportion of control cluster survey participants who accessed the intervention (degree of contamination) and 2) proportion of intervention cluster survey participants who accessed the intervention. Sociodemographic details will be collected and data on exposure to the intervention, and on duration of residence will be collected to assess in-migration, movement between clusters and likelihood of contamination.

Participants will be asked about knowledge of HIV status, history of HIV testing (including date of, place of and reason for test) and whether accessing HIV care/on ART, where they are accessing ART and ART adherence. Participants will be asked about their sexual behaviour (including VMMC (males only); pregnancy history, use of contraception and MHM (females only); and condoms (all)), and other risk behaviours such as smoking, alcohol and substance use and common mental disorders using validated tools. Blood pressure, height and weight will be measured. Participants will be provided with information about risk behaviours and those who meet pre-defined criteria for common mental disorder or harmful substance use or severe hypertension will be referred for appropriate care. All participants who do not want to disclose their HIV-status or do not have documented evidence of an HIV-positive test and want to know their HIV status will be referred to the local health facility for HIV testing and counselling. A blood sample for anonymised HIV antibody testing and an HIV VL (and drug resistance testing- will be collected. HIV VL will only be done on samples that test HIV-positive in the laboratory.

